### Study Design

Our study is a quasi-experiment with a before and after design. The interventions have both been evaluated in separate cluster RCTs (6, 22). However, our proposed studies are not conceived to be “head-to-head” comparisons of their effectiveness. The studies, rather, are *mechanism focused* and the two school-based interventions offer contrasting conditions: one leverages peer influence and the other uses a more straightforward classroom approach to deliver information. While ultimately a classroom and school based norm around smoking may change for each intervention, the change mechanism may be different.

Using a whole school year approach, our study design involves an investigation of the evolution of social networks and norms around smoking before and after a smoking prevention intervention. First, we conducted a cultural adaptation and a pilot study in three schools (one school in Northern Ireland and two schools in Colombia) with 312 pupils during 2018–2019. In 2019, in each country (Northern Ireland and Colombia) we studied ~600 pupils (aged 12–13 years/Year nine pupils in Northern Ireland and aged 12–15 years/Year seven in Colombia) in six secondary (i.e., post-primary) level schools (three receiving each intervention) exploring the contrasts between schools receiving different interventions and between countries (where norms are different).

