### Recruitment

#### Recruitment of Schools

Six post-primary schools were recruited in Northern Ireland and six in Bogotá during 2019. In Northern Ireland, schools were selected to ensure a mix of State and Catholic maintained schools, with some serving urban and rural catchments, and maximum variation sampling to ensure schools with high and low proportions of pupils eligible for free school meals. In Bogotá, six public schools from low to middle socio-economic status with maximum variation by geographic location were selected.

In Northern Ireland, relevant schools were identified from the database of schools which have previously been involved in research with the Center for Public Health and School of Education (currently over 200 schools in Northern Ireland). Schools were selected based on the sampling framework highlighted above. Schools identified as eligible were sent a letter (addressed to the school Principal or relevant senior member of staff) outlining the purpose of the study and inviting them to take part. A follow-up phone call by a member of the research team, ~1 week after delivery of the invitation letter, provided further details and an opportunity to answer any questions. For those schools agreeing to take part, a study pack was delivered providing further details about the study and role of the school.

In Bogotá, the sampling of schools followed these steps. First, a list of 40 private and public schools were prioritized based on health risks by the Education and Health Departments of Bogotá. Second, from this list, 13 schools were invited to participate according to the following inclusion criteria: (1) schools in an urban area; (2) including boys and girls; (3) having an enrollment of between 90 and 150 students in 7th year. Third, only six schools accepted the invitation and were selected for the final sample. These schools were assigned randomly to each of the interventions. Three schools were assigned to the ASSIST (*Entre Parceros*) intervention, and the other three were assigned to the Dead Cool (*Bacan*í*simo*) intervention. Schools identified as eligible were visited multiple times and researchers presented the outline of the study to the school Principal and to relevant members of staff, and invited them to take part. For those schools agreeing to take part, a study pack was delivered providing further details about the study and role of the school.

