#### Recruitment of Participants

For each school recruited, we aimed to recruit all classes in a single year group (~*N* = 80–100 on average per school; study *N* = ~600 for each country). In each school, we targeted Year 9 pupils in Northern Ireland and Year 7 in Bogotá, who were 12–13 years old. All pupils in the school year were invited to participate. Prior to the conduct of the Game Theory Experiments, each school was given Teacher Information Sheets, Pupil Information Sheets, Parent/Guardian Information Sheets, Pupil Consent Forms, and Parent/Guardian Opt-Out Forms (providing information about the study). All pupils were required to complete Consent Forms indicating whether they agree or decline to participate. In Northern Ireland, Parents/Guardians who did not wish their child to take part were asked to return completed Opt-Out Forms.

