### Statistical Methods

#### Elicitation of Social Norms and Social Network Analyses

Injunctive social norms will be modeled quantitatively, such that a decision maker's “pay-off” u(a_k_) from a set of actions V {π(a_k_)} is related to the parameter γ ≥ 0, representing the degree to which the individual cares about adhering to social norms, in: u(a_k_) = V {π(a_k_)} + γN(a_k_), with the function N capturing the social norm, [i.e., the social appropriateness of action a_k_ denoted by N(a_k_)]. We let N_g_(a_k_) denote the social norms for group *g*, estimated from the Coordination games. γ is the key parameter reflecting individual sensitivity to the norm, estimated using the total number of balls allocated to the blue “rule following” bucket in the RF task. The Dictator and Coordination games allow us to identify norms related to prosocial behavior and to smoking related activities in the target population. We can then explore whether the norms related to smoking actually do change and whether data from the RF experiments help us predict who is more sensitive to following those changed norms after the intervention. We will also measure correlations (Spearman's rank correlation) between an individual's norms-sensitivity parameter and his/her decisions in the Donation game. We will use tobit regressions that allow for censoring, regressing the distance (Δ_SNdist_) between an individual's choice and the observed average norm (average Dictator choice) in the relevant reference group on his/her norm-sensitivity parameter. The tobit regression allows us to see if there is a statistically significant relationship between norm-sensitivity and the changed norms after the intervention. We will use similar techniques when examining social norms related to tobacco use and individuals' abilities to identify them in the Coordination game. For each behavioral vignette (whose appropriateness is rated), we will calculate a correlation between individuals' norms-sensitivity parameters, and their chosen score on the social appropriateness scale, after calculating (Δ_SNdist_). Scores on the appropriateness scale are categorical, requiring ordered probit regressions. We will conduct the above analysis both pre- and post-intervention but since we will have two observations for each individual, we will use the respective panel random effects versions (including a dummy variable to identify post-intervention observations). In all regressions, we will calculate standard errors clustered on school classes. We will account for individual participants' demographic and psychosocial characteristics, and dummy variables signifying intervention type (ASSIST or Dead Cool intervention) and country (Colombia or Northern Ireland).

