
${\text{H}}_{0}^{1}$**: that individual psychosocial traits and susceptibility to social norms are independent**: After checking distributional assumptions, multiple linear regression (and where appropriate analysis of variance; ANOVA) will be employed, with any necessary transformations of raw variables; a sample size of 600 in each country achieves 80% power to detect a correlation coefficient of 0.16 for the association between susceptibility to social norms and a continuous psychosocial trait, after adjusting for a design effect of 1.99, assuming a sample of 100 per school and intra-class correlation coefficient (ICC) = 0.01.

${\text{H}}_{0}^{2}$**: that the individual social norms susceptibilities among friendship cliques are uncorrelated**: the analytic approach in this case will be similar to that for ${\text{H}}_{0}^{5}$ which is illustrated in the section sample size for the purpose of power calculation.

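### Standard errors are clustered on school classes in all regressions, but intervention and country vary only between schools, so tests of those two terms are anti-conservative whenever school-level variance exists

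*Protocol article*

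**What the plan says.** Under Elicitation of Social Norms and Social Network Analyses, the article fixes one rule for the tobit, ordered probit and panel random-effects models: "In all regressions, we will calculate standard errors clustered on school classes". The next sentence adds covariates to those models, among them "dummy variables signifying intervention type (ASSIST or Dead Cool intervention) and country (Colombia or Northern Ireland".

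Both dummies are school-level variables. Recruitment of Schools reports: "Six post-primary schools were recruited in Northern Ireland and six in Bogotá during 2019", with three schools per intervention in each country. For Bogotá it adds: "These schools were assigned randomly to each of the interventions". Within each school "we aimed to recruit all classes in a single year group", so several classes share one school and one intervention.

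The H0-1 power statement takes a different cluster. Its sample size is given "after adjusting for a design effect of 1.99, assuming a sample of 100 per school and intra-class correlation coefficient (ICC) = 0.01".

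For H0-4, which compares change in smoking-related norms between ASSIST and Dead Cool schools and between the two countries, the article promises a regression approach that allows for multilevel clustering. It does not say which levels.

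**The concern.** A cluster-robust standard error is valid for a regressor only if the clusters are independent of one another given the model. For a regressor that is constant within schools, clusters smaller than the school do not meet this condition when schools differ. Here 12 schools with, say, four classes each would be treated as 48 independent units for a contrast that has 12.

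The article gives reasons to expect school-level variance. It assumes a school ICC of 0.01 for H0-1. The Dead Cool section reports unexplained heterogeneity between schools in that intervention's effects, and school-level heterogeneity in network effects on smoking in the team's own observational study. The coordination games pay pupils for matching the most common answer in the year group, and ASSIST peer supporters work across the year group. Both features link classes within a school.

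At stake are the intervention and country terms. If their intervals are too narrow, a chance difference between a few schools could be read as a difference between interventions or countries in how norms change.

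**Working it through.** **Inputs.** From the article: 12 schools, six per country and three per intervention per country; 100 pupils per school and ICC 0.01 (H0-1); 600 per country; r = 0.16; 80% power. Assumed, because not stated: four classes of 25 per school (three of 30 and five of 20 as alternatives), two-sided 5% tests, total variance 1, equal cluster sizes.

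**Step 1: reproduce the article's figure.** Design effect = 1 + (100 − 1) × 0.01 = 1.99. Effective N = 600 / 1.99 = 301.5. Power for r = 0.16 by Fisher's z = Φ(atanh(0.16) × √(301.5 − 3) − 1.96) = 79.6%. This agrees with the stated 80% and confirms that the article's own cluster is the school.

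**Step 2: variance of a school mean, true and as implied by class clustering.** Let s be the school variance, c the class variance, e = 1 − s − c, C the number of classes and m the pupils per class.
- True: s + (c + e/m)/C
- Implied by class clustering, approximately: (s + c + e/m)/C
- Approximate type I error: 2 × [1 − Φ(1.96 × √(implied/true))]

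With s = 0.01, c = 0, C = 4, m = 25:
- True = 0.01 + (0.99/25)/4 = 0.0199
- Implied = (0.01 + 0.0396)/4 = 0.0124
- Ratio = 1.60, type I error about 12%

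With s = 0.005, c = 0.005:
- True = 0.005 + (0.005 + 0.0396)/4 = 0.01615
- Implied = (0.01 + 0.0396)/4 = 0.0124
- Ratio = 1.30, type I error about 9%

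With s = 0 the ratio is 1.00 and the formula gives 5%.

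**Step 3: simulation under the null.** This used 20,000 runs per setting, 12 schools, a linear model with intervention and country dummies, and class-clustered sandwich errors with a normal reference. The formula ignores the few-cluster bias of the sandwich estimator, so the simulated rates are somewhat higher.

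| School ICC / class ICC | 4 classes of 25 | 3 of 30 to 5 of 20 |
|---|---|---|
| 0 / 0.01 | about 6% | 6–7% |
| 0.005 / 0.005 | about 10% | 10–11% |
| 0.01 / 0 | about 14% | 13–15% |
| 0.02 / 0 (illustrative) | about 20% | 18–21% |
| 0.05 / 0 (illustrative) | about 28% | 24–31% |

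Using a t reference on the number of classes minus 1 lowers these figures by only about 1 to 2 percentage points.

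**Step 4: alternatives in the same simulations.** School-clustered sandwich errors give about 11% with a normal reference and 7–8% with t on 11 df. Regressing school means on intervention and country leaves 12 − 3 = 9 df, and its t test holds about 5% in every setting.

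**The case against.** The strongest objection is that H0-4, where intervention and country are actually compared, has its own sentence on method. Multilevel data here most naturally means pupils in classes in schools, and a hypothesis-specific statement can be read as governing. This stands in part: a school effect for H0-4 may be intended. But the sentence names no level, and the rule for all regressions is not qualified, so an analyst could cluster on class alone and comply with both. The random effects in the general paragraph do not settle it, because they are introduced for the two observations per pupil.

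Second, the main coefficient in the general paragraph is norm sensitivity, and intervention and country enter as adjustment terms. This stands. A reader might infer that the norm-sensitivity results are invalid too. The article does not support that, because sensitivity varies between pupils within classes and its standard error is much less affected.

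Third, the ICC of 0.01 is stated for H0-1, not for change in norms, where stable school differences cancel. This stands: 14% is conditional on the stated assumptions and cannot be read as the error rate of H0-4.

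Fourth, the study is a proof of concept and is expressly not a head-to-head comparison of effectiveness; its quantitative results are also triangulated with qualitative data. That lowers the stakes, but H0-4 is still a formal null hypothesis about interventions and countries.

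A reader might also object that three schools against three within one country can hardly reach significance in a permutation test. The article specifies neither such a contrast nor such a test, so this is no fault of the plan.

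**Conclusion.** The point holds for the intervention and country terms. The stated clustering level is below the level at which both vary, so their tests are anti-conservative whenever schools differ beyond their classes. It also disagrees with the unit used in the article's own power calculation. This is a rule stated wrongly, not a detail left to a later plan.

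The size is conditional. With four classes of 25, type I error is about 14% with a school-level ICC of 0.01, about 10% if that ICC is split equally between school and class, and about 6% without school variance beyond class. With three to five classes, the first two figures become 13–15% and 10–11%. The number of classes and the ICC for change in norms are not in the document.

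A reader might infer that every between-school interval, including those for H0-4, is certain to be too narrow. The text does not go that far: the H0-4 wording may cover a school effect, and the size of any fault depends on an unknown variance. What it does establish is that the two statements must be reconciled and the school level named.

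**What to change.** For intervention and country terms, including H0-4, replace clustering on classes with the school as the inferential unit and a method suited to 12 clusters. Either of these would serve:

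- school-mean change regressed on intervention and country, with t tests on 9 df;
- a mixed model with random effects for school and for class within school, with Satterthwaite or Kenward-Roger degrees of freedom.

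For the tobit and ordered probit models, use a school-level wild (score) bootstrap for these terms. State in the H0-4 paragraph which levels are modelled, so that it agrees with the general rule.

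Merely moving the sandwich estimator from class to school is not enough: with 12 clusters it still gives about 7–11%. Permutation of interventions within country is not a general substitute. It cannot test the country term, and it rests on random assignment, which is stated for Bogotá but not for Northern Ireland.

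The cost is a change of wording and wider intervals for between-school contrasts. No new data are needed.

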How are individual psychosocial and cognitive traits at baseline related to individual sensitivity to social norms? (**H**_**0**_^**1**^: that they are independent);How does individual sensitivity to social norms cluster among friendship cliques and across school year groups? (**H**_**0**_^**2**^: that the individual social norms sensitivities among friendship cliques are un-correlated);How are average social norms, measured at the classroom and year group level, affected by social network structures? (**H**_**0**_^**3**^: that social norms and social network structures are independent);After each intervention: how are changes in attitudes, intentions and behaviors toward smoking related to social norms sensitivity at the individual level, and to average social norms at the class and year group level? (**H**_**0**_^**4**^: that the changes in smoking related attitudes, intentions, and behaviors are independent of norm-sensitivity at the individual level and the same in schools which offered each intervention);After each intervention: have smoking-related social norms changed and how are these changes correlated among friendship cliques? (**H**_**0**_^**5**^: that any changes in social norms are independent among members of the same friendship clique; we assume that there will be little change in measures of homophily across one semester).

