${\text{H}}_{0}^{3}$**: that social norms at the class and year group level are independent of social network structure**: a novel aspect of this proposal is that we will examine how social norms sensitivities (Δ_SNdist_) cluster among friendship groups (before and after the two interventions), and thus examine possible mediating mechanisms for the intervention effects and whether they are moderated by social network structure. We will extend the clustering method presented by Grimmer and King (70), using a Markov Chain Monte Carlo (MCMC) model to integrate various attributes of the students and their social norms sensitivity parameters in the first step of the *a posteriori* clustering selection framework. Examining the influence of individual student attributes (their norms sensitivities; psychosocial traits like self-efficacy, and the number of family members who smoke) within a MCMC framework permits inference based on well-known expectation and maximization algorithms. We note that peer influence was inferred using hidden Markov models (7) applied to *before* and *after* data from three ASSIST schools, but with a similar per country sample size as Steglich et al. (7), we will obtain superior experimental measures of norms and thus populate the MCMC models with real rather than inferred parameters. If homophily is not stable over one semester, in a sensitivity analysis we will use an instrumental variable approach, instrumenting on orthogonal characteristics of students not nominated by the ego but who were friends of their friends, using characteristics that should not plausibly predict the egos' norms sensitivity (Δ_SNdist_), nor friendship structure (71).

${\text{H}}_{0}^{4}$**: that the changes in smoking related norms are the same in schools which were offered the ASSIST intervention and in those which were offered the Dead Cool intervention**: we will use a regression based approach permitting adjustment for the multilevel clustered nature of the data, comparing the change in smoking related norms (identified through the Coordination games) in ASSIST and Dead Cool Schools and between UK and Colombian Schools.

${\text{H}}_{0}^{5}$**: that any changes in social norms are independent among members of the same friendship clique**: see section sample size.

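### H3 is a null about class and year-group average norms, but the analysis stated under it clusters pupil-level quantities among friends and does not bear on that null

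*Protocol article*

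**What the plan says.** The research questions at the end of the Introduction (The Role of Game Theory Experiments in Studying Social Norms and Peer Influence) put the third question as "How are average social norms, measured at the classroom and year group level, affected by social network structures". The Statistical Methods section (Elicitation of Social Norms and Social Network Analyses) restates the null as "that social norms at the class and year group level are independent of social network structure".

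Under that null the stated work is: "we will examine how social norms sensitivities (Δ_SNdist_) cluster among friendship groups (before and after the two interventions". The model is a clustering method extended by MCMC "to integrate various attributes of the students and their social norms sensitivity parameters in the first step". A sensitivity analysis by instrumental variables, for use if homophily proves unstable, also concerns the norm sensitivity of the individual pupil.

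The second question is "How does individual sensitivity to social norms cluster among friendship cliques and across school year groups", and its method is given by cross-reference: "the analytic approach in this case will be similar to that for" H5.

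The same Statistical Methods section supplies a group-level quantity: "We let N_g_(a_k_) denote the social norms for group *g*, estimated from the Coordination games". It also defines two pupil-level quantities: γ, the individual's sensitivity, taken from the Rule Following task; and Δ_SNdist, the distance of the individual's choice from the average norm of the relevant reference group.

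**The concern.** The hypothesis and its analysis differ in outcome and in unit. H3 asks whether the average norm of a class or year group goes with the structure of its network. The analysis asks whether pupils who are friends resemble one another on an individual measure. Friends can resemble one another strongly while group averages are unrelated to network structure, and the reverse can also occur.

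If the plan is followed as written, the result filed under H3 cannot reject the H3 null. One of five main research questions would then be answered by a result on a different question. A reader could also carry the pupil-level sample sizes over to a statement about groups, of which there are few.

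**Working it through.** **1. Outcome, unit and network term, side by side**

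| | Outcome | Unit | Network term |
|---|---|---|---|
| H3 as worded | average norm | class, year group | network structure |
| Analysis stated under H3 | Δ_SNdist or sensitivity | pupil | friendship group |
| H2 as worded | sensitivity | pupil | friendship clique |

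The second row shares its unit with the third row, not the first. Its outcome is also that of the third row if sensitivity means γ.

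**2. Does the choice of pupil-level variable rescue H3?** The H3 paragraph attaches the symbol Δ_SNdist to the word sensitivities, whereas the definitions earlier in the section reserve sensitivity for γ. Take each in turn.

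- γ comes from the Rule Following task and contains no information on the level of any smoking norm.
- Δ_SNdist is measured from the reference group's average, so that average is subtracted out. A constructed example on the six-point scale: year group A rates 1, 2, 3 (mean 2) and year group B rates 4, 5, 6 (mean 5). Distances from the group's own mean are −1, 0, 1 in both. The norms differ by 3 points and the distances are identical.
- If the reference group is the year group, a class's mean signed distance would show how far the class lies from its year group. The H3 paragraph proposes no such aggregation.

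**3. Does another stated analysis relate N_g to network structure?**

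- H1: psychosocial traits against individual sensitivity.
- H2 and H5: correlation among members of a friendship clique.
- H4 in the methods: change in smoking norms by intervention and by country.
- Tobit and ordered probit regressions: distance or appropriateness rating against γ.
- Mediation analyses: psychosocial traits as mediators between intervention and norms.

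None does.

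**4. How many units a group-level H3 would have.** Study Design gives six schools per country, and Recruitment of Participants gives a single year group per school. That is 6 year groups per country and 12 in all.

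The plan states no power for H3, so there is no figure to reproduce. For illustration, take a simple correlation of a group-mean norm with one network measure, two-sided 5%, 80% power. Fisher's z gives

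r = tanh[(1.96 + 0.84) / √(n − 3)]

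- n = 12: 2.80 / √9 = 0.93, r ≈ 0.73
- n = 6: 2.80 / √3 = 1.62, r ≈ 0.92

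The number of classes is not given. Assuming 3 to 5 per school (36 to 60 classes) and, optimistically, independence within schools:

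- n = 36: 2.80 / √33 = 0.49, r ≈ 0.45
- n = 60: 2.80 / √57 = 0.37, r ≈ 0.36

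**5. The neighbouring power statements.** The H1 figure uses 600 pupils per country with a design effect of 1 + 99 × 0.01 = 1.99, hence 600 / 1.99 ≈ 301.5 effective pupils. Power for r = 0.16 is then 79.6% by Fisher's z, which agrees with the stated 80%. The H5 figure (300 pupils, slope 0.16) comes to 79.4% by Fisher's z or 79.9% by a t test of the slope, close to the stated figure of over 80%. Both count pupils and neither addresses H3.

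**The case against.** The strongest defence is that Δ_SNdist is not γ. It is built from the group's average norm, so asking whether departures from that norm are patterned by friendship is a recognisable, if indirect, way of asking whether norms and networks are connected, and it is not the H2 question. This stands in part. Overlap with H2 depends on which variable is meant, so a flat charge of duplication is not supported. But a pattern of departures around a group average still does not tell us whether the average itself varies with structure.

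Secondly, friendship groups are a form of network structure, and the paragraph mentions moderation by network structure and uses friends of friends as instruments. It would be wrong to say that the analysis has no network term. What is missing is the group norm as the outcome. The moderation clause, also found where the analysis is said to show how sensitivities "cluster among friendship groups (before and after the two interventions), and thus examine possible mediating mechanisms for the intervention effects", concerns intervention effects and their mechanisms.

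Thirdly, a reader might infer that H3 is never tested. A condensed article cannot show that, because a fuller protocol or analysis plan may hold a group-level analysis. The supportable statement is that no analysis stated here tests it. This is still more than an omission, because an analysis is stated for H3 and it targets something else.

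Fourthly, a reader might take the detectable correlations as exposing an inflated power claim. They contradict nothing: the power statements concern H1 and H5 (and H2 only by analogy), and the Sample Size section presents its own as an exemplar for a proof of concept study.

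Lastly, moving H3 to a class-level regression looks natural but has its own unit problem. Coordination-game payments reward matching the year group, and friends are nominated from a school year roster.

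**Conclusion.** The point holds as a mismatch between hypothesis and stated analysis. H3 concerns average norms of classes and year groups. The analysis under it is pupil-level whichever of the two variables is meant, and no analysis stated in the article sets N_g against network structure. A positive clustering result would not bear on the H3 null. This rests on the text alone and needs no assumption. Repetition of H2 follows only if γ is the variable used.

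The figures of 0.73 for 12 year groups and 0.92 for 6 are illustrative. They assume a simple correlation with one network measure, and they show only that a group-level H3 is exploratory at this size. The matter touches one of five main research questions in a proof of concept study and is cheap to put right.

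**What to change.** 1. Present the friendship-group clustering as a pupil-level question, either under H2 or as a reworded H3. Use one variable and one name throughout: γ for sensitivity, Δ_SNdist for distance from the norm. If H2 and H3 both remain pupil-level, say how they differ.

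2. For H3 as worded, relate N_g (the mean Coordination-game ratings, at each wave) to network measures from the roster nominations, for example density, reciprocity and in-degree centralisation. Do this at year-group level, where norms were incentivised and ties nominated. Report it descriptively, with n = 12 (6 per country).

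3. Label any class-level regression (school as a random effect, country as a fixed effect) exploratory, because class means reflect beliefs about a year-group norm and class networks cut ties between classes.

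The cost is some rewording and one small analysis of ratings and nominations that data collection already covers. The downside is that H3 is openly exploratory and can detect only large associations.
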